### Aim

In this study, we aim to establish a large patient experience evidence base, and characterise the key challenges and opportunities to improve survival and quality of life for women in LMICs. We will test our hypothesis that key factors vary by country, requiring bespoke potential health strategies. With the evidence obtained from this study we expect to raise the profile of ovarian cancer in LMICs. We hope to enable national teams to engage governments and health policy makers; secure extra funding for diagnostics, research and awareness campaigns; and improve support for women. Examples of this type of approach have been successfully undertaken in high-income countries [25–28].

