### Study infrastructure

To reach sufficient participants and maximise their ability to participate, the OC proposed collaborating with a selection of clinicians treating women with ovarian cancer either known to the Coalition, or through the extensive network of IGCS members. An initial target list of 31 LMICs was drawn up and approaches made to clinicians and national and regional gynecologic oncology societies. In total, 113 clinical sites have been recruited using snowballing methods across 24 countries (Fig 1). Classification of country income level was determined using the World Bank open data, accessed in June 2021 [29].

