**Further analysis**		
**Outcome variables**	**Predictor variables**	**Possible confounders**
Access to chemotherapy	Age on diagnosis Family income Distance to hospital Who pays for ovarian cancer care Resource level of participating site	Stage of ovarian cancer Date of diagnosis Use of neoadjuvant chemotherapy
Access to optimal cytoreductive ovarian cancer	Age on diagnosis Family income Distance to hospital Who pays for ovarian cancer care Resource level of participating site	Date of diagnosis Use of neoadjuvant chemotherapy
Levels of awareness of ovarian cancer	Education level Family income level Distance to hospital Family history	
Time to seek help for symptoms	Age Education level Family income level Who pays for ovarian cancer care First person consulted re symptoms Number of visits prior to diagnosis Level of concern over symptoms Type of symptoms Number of symptoms	

We will perform descriptive and inferential statistics, overall and by country and economic grouping using statistical softwares such as STATA and R. Categorical variables will be summarised with counts and percentages, with Chi Squared Tests or Fisher’s Exact Test used to compare proportions between groups. Continuous variables, such as time to diagnosis, will be examined graphically and summarised using appropriate metrics (mean and standard deviation or median and interquartile range depending on the distribution of the variable data). Tests, such as Kruskal-Wallis, will be applied to continuous variables. Outlying countries will be identified and described.

Appropriate regression analysis approaches will be used to examine assocations between independent and outcome variables. Binary, ordinal or nominal regression will be used depending on the nature of the outcome variable. Univariable regression will be employed to examine individual associations and multivariable regression to examine combined assocations between predictor and outcome variables.

The two free-text answers will be translated, coded and analysed using qualitative content analysis to identify categories and possible themes.

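### The named group-comparison tests treat women as independent although they are nested in 113 sites and 24 countries, so evidence for income-group and region effects is overstated and country comparisons ignore site-to-site variation

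*Protocol article*

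**What the plan says.** The Aim section states a hypothesis to be tested: "We will test our hypothesis that key factors vary by country". The Data analysis section says that variation in key metrics will be examined by country, region and socio-economic country group, and promises inferential as well as descriptive statistics. It then names the methods:

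- Categorical variables: "Categorical variables will be summarised with counts and percentages, with Chi Squared Tests" or Fisher's Exact Test used to compare groups.
- Continuous variables: "Tests, such as Kruskal-Wallis, will be applied to continuous variables. Outlying countries will be identified and described".
- Regression: "Appropriate regression analysis approaches will be used to examine" associations, and "Binary, ordinal or nominal regression will be used depending on the nature of the outcome variable". Table 3 lists the resource level of the site among the example predictors.

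On structure, the Study infrastructure section says that "113 clinical sites have been recruited using snowballing methods across 24 countries", with one to 12 sites in a country. The Sample size section gives a total of 2,160 if every country reaches its minimum.

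The article does not mention clustering, random effects, robust standard errors, an intracluster correlation (ICC) or a design effect. The nearest provisions are recording the selection method for each woman (Sample selection) and sensitivity analyses by selection method (Discussion). Neither changes a standard error.

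**The concern.** Women treated at the same hospital share clinicians, referral routes, selection method and often the same questionnaire administrator. Women in one country share a health system. Their answers on time to diagnosis, access to surgery or awareness will be correlated. The article itself points this way: its hypothesis is that countries differ, and the Sample selection section abandons a single approach because resources, attendance and records differ between countries and between centres within a country.

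A chi-squared or Kruskal-Wallis test by income group counts about 2,160 independent units where the exposure varies over only 24. A test across countries counts women where the sampled units within a country are a few sites. In the first case, ordinary differences between countries can look like an income or regional gradient. In the second, ordinary differences between hospitals can appear to confirm the study's hypothesis or mark a country as outlying. The results are meant for country reports and for work with governments and policy makers, so an overstated contrast has practical consequences.

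**Working it through.** **1. The plan's own figure.** For the pooled sample the Sample size section gives 1534 women for ±2.5 points at 95% confidence. With n0 = 1.96² × 0.25 / 0.025² ≈ 1536.6 and n = n0 / (1 + (n0 − 1)/N), where N = 823,000 is the global five-year prevalence in the Introduction, n = 1533.7. The figure reproduces. It is a simple-random-sample formula, so independence is assumed at the design stage too. The Table 2 minimums add to 2,160.

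**2. Cluster sizes.** 2160/24 = 90 women per country; 2160/113 = 19.1 per site.

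**3. Design effects.** DE = 1 + (m − 1) × ICC. The ICCs are assumptions.

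| ICC | DE, country (m = 90) | DE, site (m = 19.1) |
|---|---|---|
| 0.01 | 1.89 | 1.18 |
| 0.02 | 2.78 | 1.36 |
| 0.05 | 5.45 | 1.91 |

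**4. Approximate error of the named test when there is no true effect.** An unadjusted k-group chi-squared statistic behaves roughly like DE times a chi-squared variable with k − 1 degrees of freedom. The actual error is then P(χ² > critical value / DE).

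- Income group (3 groups, 2 df, critical value 5.991): the thresholds are 3.17 / 2.16 / 1.10, giving 20% / 34% / 58%.
- Region (6 areas in Table 2, 5 df, critical value 11.07): the thresholds are 5.86 / 3.98 / 2.03, giving 32% / 55% / 84%.
- Country, site variation only (24 groups, 23 df, critical value 35.17): the thresholds are 29.8 / 25.8 / 18.5, giving 16% / 31% / 73%.

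**5. Simulation on the Table 2 minimums.** Null simulations used the actual country minimums, with 113 sites spread 4 or 5 per country.

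| Chi-squared test | Source of clustering | 0.01 | 0.02 | 0.05 |
|---|---|---|---|---|
| Income group | country ICC | 19% | 32% | 55% |
| Region | country ICC | 32% | 55% | 87% |
| Country | site ICC, no country effect | 16% | 31% | 73% |

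Repeat runs agree within about three points. At ICC 0 all the tests reject about 5%, so the excess comes from clustering. Kruskal-Wallis behaves similarly: with country and site ICC of 0.02 each it rejects 37% for income group and 61% for region. Fisher's test was not simulated but makes the same independence assumption.

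The Sample size text groups the countries 3/11/10 by income, while the rows of Table 2 count to 3/13/8. The income-group result is high under either grouping.

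**6. Smaller effects.** With site variation only, at a site ICC of 0.01 to 0.02, income-group error is about 7% to 11%. A site-level predictor such as resource level, analysed as if women were independent, has a two-group error of 7.1% / 9.3% / 15.6% at site ICC 0.01 / 0.02 / 0.05.

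**7. After the fix.** Over ICCs 0 to 0.05, tests on country means reject 4.5% to 6.0% for income group and 3.9% to 5.5% for region. A site-level analysis of variance for country rejects 4.1% to 5.2% when there is no true country variance.

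**The case against.** Several points on the other side are sound and limit the finding.

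- **Regression.** A reader might infer that the plan commits to ordinary regression without clustering. It does not. The wording is open, the model family is chosen by outcome type, and mixed or cluster-robust versions of all three families exist. An article may leave the error structure to the full plan. The finding rests on the tests that are named.
- **Table 3.** A reader might infer that the models wrongly omit country. Table 3 is introduced as giving examples, and its last column lists possible confounders, so it is not a fixed specification. Nor does the income question (Q.6 in Table 1) show confounding by country: it is scaled to the woman's own country, which tends to weaken such a link.
- **Country comparisons.** Country is the factor under test, so true variance between countries is signal. Only site variation within country creates false positives. In a single-site country no model can separate the two.
- **Target of inference.** If interest is confined to these 24 countries, differences between groups of them are real. The error lies in attributing them to income level or region in general.
- **Size.** A reader might infer that error will far exceed 5% everywhere. That depends on ICCs the article does not give, and at low site ICCs alone the inflation is modest.
- **Context.** This is an exploratory, cross-sectional convenience sample with no stated significance level, and the Discussion admits selection bias and wide country intervals. Selection may limit inference as much as the standard errors do.

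None of this rescues the named tests. They are stated as the inferential method for groups defined at country level, and nothing else in the article corrects them.

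**Conclusion.** The point holds for the named tests. Used as written, chi-squared, Fisher and Kruskal-Wallis overstate the evidence that income level or region is associated with an outcome. The three low-income countries would be treated as if every woman in them were a separate observation of the exposure. The size depends on the assumed ICC, and the inflation is substantial for both factors even at a between-country ICC of 0.01. A between-country ICC of zero would contradict the study's own hypothesis. For country comparisons the inflation comes from site variation alone, and the figures assume near-equal sites, 4 or 5 per country. The regression plan is open rather than wrong, but the site-resource predictor needs the same care. Severity: should be fixed before analysis.

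**What to change.** Change the Data analysis wording as follows.

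1. Keep Chi Squared, Fisher's Exact and Kruskal-Wallis for description only.
2. For income group and region, base inference on country as the unit: country random intercepts, or tests on country-level summaries with small-sample degrees of freedom.
3. For country comparisons and the identification of outlying countries, allow for between-site variance through site random intercepts or site-level tests. Report single-site countries as site results.
4. In pooled regressions, specify site random intercepts or site-clustered standard errors, and include country when the predictor is a patient characteristic.

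No new data are needed, since site and country are known for each woman. The cost is wider intervals and fewer significant region or income-group contrasts. Multilevel ordinal or nominal models may fit poorly with three low-income countries and some single-site countries, so name the cluster-level or cluster-robust version as the fallback.

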### Ethical considerations and declarations

The study is being conducted in accordance with the principles of the Declaration of Helsinki (2013). The protocol, survey, informed consent form, and participant information sheet have been submitted to an appropriate research ethics committee, health research authority as required in each country/site, and host institution(s) for written approval. Where necessary the CLC has submitted and obtained approval from the above parties and the Principal Investigator for all substantial amendments to the original approved documents. In three of the 24 countries, local ethics committees have made a requirement that patients be compensated for their time. This compensation level varies between US$3 and US$8 by country and is to be given on completion of the survey, with each patient receiving the same amount within a given country.

### Status and timeline of the study

At the time of writing, 24 countries are progressing with the study, with 19 actively collecting data on the REDCap platform. Some countries will stop collecting data in September 2023, but others, for whom translations, ethics approvals or local circumstances meant delayed starts or slow progress, data collection will continue up until the end of December 2023.

## Discussion

There are a number of strengths to the study. Participating countries will have the opportunity to compare key challenges and opportunities to improve survival and quality of life for women with ovarian cancer with other LMICs. For some of the teams, this is the first time they have contributed to research at their centre or been involved in collaborations with others in their country or internationally. For several countries, it provides the first dataset on ovarian cancer in their country, which could be used to inform clinical and policy decisions, drive academic research and develop interventions to improve outcomes for women with ovarian cancer. In addition, for women with ovarian cancer in many of the participating countries, this is the first time their experiences and opinions have been sought for research, bringing visibility to their plight and providing the opportunity to help other women in the same situation. Already there has been the formation of Ovarian Cancer Malaysia involving a patient member of the OC and the CLC, and a survivorship group is being planned in Kenya. The study also provides clinical staff with insights about important patient perspectives beyond treatment.

There are several limitations to the study. First, it will only capture experiences from women who have been able to afford or access a diagnosis and subsequent treatment. In some participating countries, there is just one centre that diagnoses and treats the condition so there are many economic, geographic, societal and cultural barriers preventing symptomatic women from getting medical help. Second, the varied approach of sample selection may naturally introduce biases, but it is not feasible to apply a uniform approach in all participating sites. To account for this, sensitivity analyses will be conducted by including and excluding certain selection methods where distinct patterns are observed. Third, the minimum sample size per country will only provide a broad overview with wide confidence intervals at a standalone country level. However, the regional and global analysis will be able to determine how a country differs from the others in the study with greater accuracy, helping focus priorities for action. Finally, by running the study through known contacts of the Coalition and IGCS, there may be biases in terms of women’s experiences, particularly around levels of care, as the CLC and LSL have access to training and networks of specialist clinicians.

The results of the study with analyses at global, regional, and thematic levels, will be disseminated through peer reviewed papers, with presentations at key relevant conferences. In this way it will contribute to the knowledge base on ovarian cancer globally, and in participating LMICs. It will be supported by a media outreach campaign. Each of the CLCs will be encouraged to submit papers for publication and presentations at national and regional level in local languages to extend the reach of the study and its findings. Subject to funding, the Coalition plans to work directly with some of the country teams to develop action plans and engagement with health policy makers, which will be informed by the study findings. Some of the participating countries plan to continue data collection, subject to the appropriate permissions, and/or adapt the study for other disease areas. By publishing the protocol, survey, and findings, the authors also hope to encourage other countries to consider running the study themselves.

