## Methods

### Design and setting

The study has been developed by the Coalition, in partnership with the International Gynecologic Cancer Society (IGCS). It is overseen by a global oversight committee (OC) comprising clinical and patient advocates from six geographic areas, together with additional data and diagnostic expertise.

This study adopts a low risk, observational, cross-sectional design. A standardised questionnaire, derived from a previously published set of questions used in an online survey with participants recruited via social media in 2018 [12], has been developed to explore the experiences of women with ovarian cancer in LMICs based on symptoms, route to diagnosis, treatment, and quality of life. This study is designed as a one-off interaction with no follow-up, with recruitment of women via participating hospital clinics to maximise uptake.

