### Sample selection

Initially the OC recommended a standardised single approach to sample selection, with all patients diagnosed within the last five years at a participating site being approached for inclusion in the study. This would have allowed for inclusion of survivors with a wide-spread time since diagnosis, and reached patients who might otherwise have stopped treatment or be in remission. However, given the diversity of resources, attendance patterns, and access to patient records between countries and even participating centres within a country, the OC decided a single approach was not feasible. A randomised approach was also not deemed suitable given the challenges ensuring consistency in implementation across many sites. Instead, a convenience sampling approach was approved, offering three different models listed below. To compensate for the variety of approaches, the method of sample selection will be recorded for each patient to allow for data stratification if required. CLCs suggest all participating centres in their country follow the same approach, but this is not mandated. The sample selection approaches, and associated caveats are as follows:

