The site team reviews all cases on their records that have been seen in the previous five years, with a view to contacting eligible ovarian cancer patients and inviting them to participate. This approach is dependent on availability of staff resource, accessible patient records and reliable communication methods with patients. It might also catch patients who have previously stopped treatment but may also require them to attend a new appointment if they cannot be reached by email, or WhatsApp, and so completion rates may be lower;The site team reviews all cases of ovarian cancer patients who have recently attended an appointment, working backwards in a sequential manner, until they meet the minimum or preferred sample size. This requires extra resource and good record-keeping, and may mean the sample selected is skewed to those with a more recent diagnosis; andThe site team reviews all cases of ovarian cancer patients due to attend a forthcoming appointment in person or virtually, inviting eligible patients to participate at that appointment. This approach requires less staff resources, as patient notes and attendance in clinic is already factored in. It may also improve completion rates. However, this approach may result in the inclusion of a greater proportion of patients with a more recent diagnosis, those on active treatment or experiencing complications, and can add time to clinic appointments.

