### Inclusion and exclusion criteria

The inclusion criteria for the study are as follows:

The woman with ovarian cancer is a patient at one of the participating hospitals;The woman with ovarian cancer is willing and able to give informed consent for participation in the study;The woman is biologically female, aged between 18 and 99 years at the time of recruitment;The woman has been diagnosed with any stage or type (including borderline) of primary ovarian, fallopian tube or primary peritoneal cancer within the previous five years (of the date of completing the survey); andThe woman has already been informed of their diagnosis of ovarian cancer at a previous appointment and the administrator is confident the woman with ovarian cancer understands what they have been told. If there is any doubt, the administrator must check with the clinician caring for the patient.

The participant is excluded from the study if any of the following apply:

The woman is attending the hospital or clinic to receive their diagnosis of ovarian cancer;The woman is deemed too unwell to be able to cope with the demands of filling in the survey or responding to questions;The woman is identified as being unable to cope with the demands of filling in the survey or responding to questions, or does not understand her diagnosis as a result of learning difficulties, medical conditions or mental health concerns; andThe woman has already completed the survey at a previous visit to the hospital.

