### Data collection procedure

The administrator generates a unique identifier number (UIN) for the ovarian cancer patients on REDCap and some basic demographic and clinical data is entered to determine eligibility (S6 File). This information includes age at diagnosis, month and year of diagnosis, type and stage of ovarian cancer and current treatment status. This provides an overview of women attending the clinics and allows basic comparisons between the groups who do and don’t consent.

Women with ovarian cancer are then approached and taken through an informed consent process. They are given written and verbal information about the study. If they are not attending clinics directly, they can be sent this information by email or be spoken to by phone. They are taken through the purpose and outline of the study and the risks and benefits of taking part are discussed. They are informed that they do not have to participate, they do not have to answer every question, and that they can withdraw their information up to 3 months after the close of data collection. They are then asked whether or not they consent to participate in the study and if they consent, whether they wish to i) self-complete a paper survey, ii) self-complete the survey via a secure email link, iii) self-complete the survey via a secure WhatsApp link (or other online messaging app), or iv) whether they wish to have the administrator ask them the questions. Their decision is recorded. Women who receive the information in person, or by phone need to record their consent in writing, and a copy is kept in a secure location on site. In addition to the standard consent form for the study, some local sites require patients to also complete their own informed consent forms, as part of the ethics approval. One country asked for women to consent with a thumbprint. Women who receive the information by email or WhatsApp can consent electronically at the start of the survey, or they can request an administrator contact them if they have questions before deciding.

Local teams are encouraged to supply the women with some written as well as verbal information about ovarian cancer, including at least two sources of potential support and information, be they non-governmental organisations (NGO), charities, or other groups (S6 File). The process is summarised in Fig 3.

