### Data analysis

In our analysis, we seek to examine variation in key metrics (such as stage of ovarian cancer, time to diagnosis and levels of awareness) by country, region and by the socio-economic country group. In addition, we will explore associations between patient and country characteristics and key outcome measures. Table 3 gives some examples of the outcome variables and expected areas for further analysis.

**Table 3 pone.0298154.t003:** Outcome variables and expected further analysis.

Outcome variables		
• Access to chemotherapy • Access to optimal cytoreductive surgery • Access to genetic testing • Level of ovarian cancer knowledge • Time to seek help • Time from seeking help to obtaining a diagnosis • Time from diagnosis to treatment • Information needs •Impact on family finances •Priorities for action		

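### Country, region and income-group comparisons ignore time since diagnosis, and the stated remedy (including or excluding selection methods once patterns appear) does not act on it

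*Protocol article*

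**What the plan says.** All references are to the Protocol article.

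- **Who is sampled.** Design and setting: "This study is designed as a one-off interaction with no follow-up". Inclusion and exclusion criteria admit any stage of "primary ovarian, fallopian tube or primary peritoneal cancer within the previous five years (of the date of completing the survey"). Only women who are alive and reachable through a hospital can answer.
- **How they are sampled.** Sample selection: "a convenience sampling approach was approved, offering three different models listed below". The section warns that working backwards through recent attenders may favour recent diagnoses. Of the forthcoming-appointment model it says "this approach may result in the inclusion of a greater proportion of patients with a more recent diagnosis", along with women on treatment or with complications.
- **Who chooses the model.** Study infrastructure gives the choice to the country lead clinician. Sample selection adds: "CLCs suggest all participating centres in their country follow the same approach, but this is not mandated". The method is recorded for each patient so that data can be stratified if needed.
- **What is compared.** Data analysis plans to examine key metrics, with stage, time to diagnosis and awareness as examples, "by country, region and by the socio-economic country group". The tests named are Chi-squared, Fisher's exact and Kruskal-Wallis. Outlying countries are to be singled out.
- **What is adjusted for.** Table 3 lists date of diagnosis as a possible confounder for access to chemotherapy and for cytoreduction. The confounder cells for awareness and time to seek help are empty, and stage has no row.
- **What is recorded.** Data collection procedure: "age at diagnosis, month and year of diagnosis, type and stage of ovarian cancer and current treatment status".
- **The stated remedy.** Discussion (limitations): "sensitivity analyses will be conducted by including and excluding certain selection methods where distinct patterns are observed".

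**The concern.** Time since diagnosis affects what a cross-sectional sample of survivors shows, in two ways.

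1. **Stage.** Women with advanced disease die sooner, so the further back a sample reaches, the smaller the advanced share among those still alive. Two countries with the same stage distribution at diagnosis will differ if one samples recent attenders and the other reviews five years of records.
2. **Access and time from diagnosis to treatment.** A woman surveyed soon after diagnosis may not yet have had chemotherapy, surgery or genetic testing. Unless not-yet-treated is handled explicitly, a recently diagnosed sample will appear to have less access and, among those treated, shorter waits.

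The remedy in the Discussion works on the selection method. The bias runs through time since diagnosis, which differs between methods and also varies within each. The remedy is also triggered by what the data show, so whether it is run, and which methods are dropped, is decided after the results are seen.

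At stake are the country contrasts. The Discussion expects the regional and global analysis to show how a country differs from the others and so help set priorities, and each country receives a report comparing it with the average.

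**Working it through.** **1. The plan's own precision figures.** For one proportion with p = 0.5 and a finite population correction, n₀ = 1.96² × 0.25 / e² and n = n₀ / (1 + (n₀ − 1)/N).

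- Global, e = 0.025, N = 823,000 (Introduction): n₀ = 1536.6, n = 1533.7, which matches the stated 1534.
- Country example, Kenya, e = 0.10, N = 2314 (Table 2): n₀ = 96.0, n = 92.2, which matches the stated 92.

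The ±10 and ±2.5 points are therefore sampling margins only, and are the yardstick for the bias below.

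**2. Stage: effect of the recruitment window alone.** Inputs:

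- Advanced share at diagnosis 65%, the same in every country (the Introduction says nearly two-thirds).
- Five-year survival by stage is *assumed*, because the document gives none: 20–50% advanced, 80–90% early, identical in both countries.
- Exponential survival, with diagnosis dates uniform over the last T years.

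With h = −ln(S₅)/5, the relative number alive in a stage is (1 − e^(−hT))/h. The advanced share among survivors is 0.65·A(T) / (0.65·A(T) + 0.35·E(T)), where A and E are that quantity for advanced and early disease.

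Worked case, S₅ = 30% advanced and 85% early:

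- T = 1: 0.65 × 0.889 = 0.578; 0.35 × 0.984 = 0.344; share 62.7%.
- T = 5: 0.65 × 2.907 = 1.890; 0.35 × 4.615 = 1.615; share 53.9%.

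| Assumed S₅ advanced / early | Implied overall S₅ | T = 1 y | T = 5 y | Spurious gap | Chance significant, 90 per group | 500 per group |
|---|---|---|---|---|---|---|
| 50% / 90% | 64% | 63.7% | 58.5% | 5.1 | 0.11 | 0.38 |
| 40% / 90% | 57.5% | 63.2% | 56.2% | 7.0 | 0.16 | 0.62 |
| 30% / 85% | 49% | 62.7% | 53.9% | 8.7 | 0.22 | 0.80 |
| 20% / 80% | 41% | 61.9% | 50.7% | 11.1 | 0.32 | 0.95 |

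Implied overall S₅ is 0.65 × advanced + 0.35 × early. The Introduction puts overall survival below 50%, so only the last two rows agree with it, and they give the larger gaps. The 500 per group is an assumed regional size.

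One year against five is the widest contrast. Two years against five (T = 2 shares 62.4, 61.4, 60.4 and 58.9%) gives gaps of about 4 to 8 points.

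**3. Access: effect of the window.** All inputs are assumed: 85% eventually treated, lognormal wait with median 45 days and log-SD 0.8, survey time uniform from day 7. Apparent access is 0.85 × the average of Φ((ln t − ln 45)/0.8) over the survey times t.

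- Diagnoses over the last 180 days: 60%, and the median wait among those treated is 36 days.
- Diagnoses over the last 1,825 days: 82%, median 44 days.
- Only women at least 180 days from diagnosis: 84% (180–365 days) against 85% (180–1,825 days). Most of the artefact disappears.

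**4. Can the method effect be separated from the country effect?** A model with 24 country terms and 2 method contrasts has 26 parameters. If every country used one method, the design matrix has rank 24 and the method effect cannot be estimated. With two methods in every country the rank is 26 and it can. The actual mix lies somewhere between and is not given.

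**The case against.** The case on the other side is substantial, and several stronger readings fail.

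- **A reader might infer that method largely coincides with country, so the sensitivity analysis cannot work.** The documents do not say so. One approach per country is suggested, not required, and the realised mix is not reported. Restricting to one method still allows a like-with-like comparison among the countries that used it, and mixed countries give within-country contrasts. What stands is that the remedy is weak where a country used one method.
- **A reader might infer that access and time to treatment will be summarised as complete data.** That is not stated. The questionnaire is in a supplement that is not shown and may allow a not-yet answer. The forthcoming-appointment model is also said to over-represent women on active treatment, which weakens the assumption that its recent patients are untreated. Time to diagnosis is complete for every diagnosed woman, so the censoring argument does not reach it.
- **Date of diagnosis is not ignored.** It is a candidate confounder in both access regressions shown in Table 3, and that table is presented as examples. The protocol also discloses the skew, records method and diagnosis date, and plans a review of each country's data for local bias. What stands is that the group tests named for the country comparisons carry no such adjustment.
- **Making women within 12 months of diagnosis the main stage analysis would be a poor trade at country level.** Take five-year survival of 35%/90% in one country and 10%/70% in another. Of 90 women in each, about 23 and 28 fall within 12 months. The apparent gap drops from 8.5 points (54.8% against 46.3%) to about 2 (62.9% against 60.7%), but the 95% half-width for the difference grows from 15 to 27 points. Root mean squared error rises from 11.3 to 13.8 points. It falls only with much larger samples (350 per country: 9.3 to 7.3).

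**Conclusion.** The point holds in a limited form. The planned comparisons between countries, regions and income groups use unadjusted tests on women alive up to five years from diagnosis, while the protocol itself expects its selection models to differ in how recent the diagnoses are. The remedy it names is data-triggered and does not act on time since diagnosis.

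Under assumed stage-specific survival, and with no true difference between countries, the recruitment window alone can produce about 5 to 11 points in advanced stage. A minimum-size country would rarely show this as significant, but a regional or income-group comparison often would. The size depends on the survival assumptions, on uniform diagnosis dates and on a wide contrast in windows. The direction depends only on advanced disease having poorer survival. The access figures rest wholly on assumed waits and show the mechanism rather than an expected size.

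This is an inexpensive improvement to the analysis of a survey that already discloses selection bias. It does not show that the comparisons are unusable.

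**What to change.** 1. Adjust, stratify or standardise all country, region and income-group comparisons for time since diagnosis, computed from the recorded month and year of diagnosis and the survey date.
2. For access and time from diagnosis to treatment, either limit the comparison to women far enough from diagnosis to have had treatment, or treat those not yet treated as censored at the survey date. Fix the choice and any cut-off before analysis.
3. Run the selection-method analysis in every case rather than when patterns appear. Report how many women each country recruited by each method, and use within-country contrasts where a country used more than one.
4. Report stage among women surveyed within 12 months of diagnosis as a sensitivity analysis, mainly at regional and income-group level, where numbers allow.
5. Add to the limitations that women who died before sampling are missing. Adjustment for time since diagnosis does not restore them; item 4 only lessens the problem.

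**Cost:** analysis wording and one added limitation. The diagnosis date and selection method are already collected. Intervals will be somewhat wider, and the 12-month stage analysis will be imprecise for single countries.
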